## Abstract

**Background:**

Anterior knee pain may occur after total knee arthroplasty (TKA). Patellar resurfacing, which is considered to lower the incidence of anterior knee pain after TKA, remains controversial. In the present study clinical and radiological outcomes after TKA performed on patients with clinical and radiological signs of femorotibial and patellofemoral osteoarthritis (OA) with and without patellar resurfacing will be compared.

**Methods/design:**

Fifty patients will be included in a randomized controlled trial. Patients scheduled for TKA with clinical and radiological signs of femorotibial and patellofemoral OA will be included. Arthritis of the patellofemoral joint was determined based on the preoperative Baldini and Merchant X-ray views, which is assessed by the orthopaedic surgeon who treats the patient. Exclusion criteria are rheumatoid arthritis, history of patellar fracture, tuberosity transposition, high tibial osteotomy (HTO), hip arthroplasty and posterior cruciate ligament insufficiency. Patients will be randomized to undergo TKA either with or without patellar resurfacing. Outcomes will be assessed preoperatively, at 6 weeks and at 6, 12, 18 and 24 months postoperatively. Primary outcome measure is the patellofemoral scoring system according to Baldini. Secondary outcome measures are the Knee Society clinical rating system (KSS) and the Knee Osteoarthritis Outcome Scale (KOOS) scores. Conventional weight-bearing radiographs, and views according to Baldini will be used to asses component loosening, wear, and patellofemoral problems including fracture or loosening of resurfaced patellae, subluxation and wear of non-resurfaced patellae.

**Discussion:**

There is no consensus regarding patellar resurfacing during primary TKA. Current prospective studies fail to determine any differences in clinical outcome among patients after TKA with or without patellar resurfacing. This randomized controlled trial has been designed to determine the effectiveness of patellar resurfacing during TKA in patients undergoing TKA who have clinical and radiological signs of tibiofemoral and patellofemoral OA, using a specific patellofemoral outcome measurement.

**Trial registration:**

Netherlands Trial RegistryNTR3108

**Electronic supplementary material:**

The online version of this article (doi:10.1186/1471-2474-15-358) contains supplementary material, which is available to authorized users.

## Background

Total knee arthroplasty (TKA) is a well-established surgical procedure, effective for relieving pain and improving function in patients suffering from osteoarthritis of the knee (OA)[1]. Studies have shown that more than 90% of modern primary total knee arthroplasties survive for at least ten years[2, 3]. Nonetheless, a substantial number of patients remains who have patellofemoral pain following TKA[4, 5]. Resurfacing of the patella is considered to be effective in lowering the incidence of anterior knee pain[6, 7]. Indications for patellar resurfacing during primary TKA, as described in current literature[8–11], include older age, anterior knee pain or other patellofemoral symptoms, rheumatoid arthritis (RA), obesity, history of patellar subluxation or dislocation, large and/or thick patella, a multi-operated knee joint and major loss of patellofemoral articular cartilage noted intraoperatively.

Patellar resurfacing is not without drawbacks. Complications of patellar resurfacing include patellar fracture, tendon rupture, osteonecrosis and soft-tissue impingement[12–15]. Unsatisfactory results because of patellar tilt, maltracking, instability, polyethylene wear and patellar clunk syndrome have been reported[16, 17]. Unresurfaced patellae are subjected to high compressive forces, and may develop cartilage erosion after knee joint replacement[18]. No studies found conclusive evidence that patellae affected by such changes become symptomatic after TKA[19, 20].

A meta-analysis including 1223 knees showed a 14% reduction in the absolute risk of postoperative anterior knee pain following patellar resurfacing during primary TKA (95% CI: 6–21%)[21]. By resurfacing the patella during primary TKA the risk of secondary patellar replacement was lowered by 5%[6]. Recent reports fail to demonstrate benefits of patellar resurfacing regarding functional outcome. Some reports have demonstrated that secondary patellar resurfacing after TKA leads to inferior results compared to initial patellar resurfacing during primary TKA[22–24]. Other prospective studies fail to determine any difference in clinical and functional outcome among patients after TKA with or without patellar resurfacing[8, 11, 25, 26]. A recent randomised controlled trial (RCT) including 1715 knees showed no significant difference in functional outcome between patellar resurfacing or non-resurfacing during TKA (95% CI: -0.58–1.76) using the Oxford Knee Score[27].

The inability to detect clinical differences may be caused by our lack of identifying those individuals who are thought to benefit from patellar resurfacing whilst avoiding potential complications[28]. Furthermore, current scoring systems are unable to detect subtle differences in specific patellofemoral pain and function.

The aim of the present study is to create a selective cohort of patients with clinical and radiological signs of femorotibial and patellofemoral knee OA who are indicated for TKA. All patients will be scored through the recent developed Baldini tool, a validated scoring system specifically designed to evaluate the patellofemoral joint[29, 30]. The hypothesis is that in our cohort of patients patellar resurfacing will show more than 10% improvement in the Baldini score compared to patients without patellar resurfacing 24 months after TKA. This paper reports on the study design of the PATRES (PATellar RESurfacing) trial.

## Methods and design

### Study design

The study design is a randomized controlled trial: patients will be randomly allocated to have TKA with or without patellar resurfacing. The study will be conducted at the Department of Orthopaedic Surgery of Martini Hospital Groningen, the Netherlands, a secondary referral teaching hospital. One investigator will enroll the patients. Two orthopaedic surgeons will perform the procedure, and are thus not blinded. One independent investigator, not involved with enrollment or surgical procedure, will evaluate the outcome measurements. This investigator and all patients will remain blinded through the assigned regimen. The study has been approved by a Medical Ethics Committee, and is also registered in the Netherlands Trial Registry [Reference NTRTC3108].

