### Main study parameter/endpoint

Primary outcome measure is the patellofemoral scoring system by Baldini et al. This tool represents patellofemoral kinematics more accurately, and may explain related patellofemoral complaints better[30]. The scoring system includes objective and subjective aspects concerning the patellofemoral joint, ranging from 0 (worst) to 100 (best)[30].

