**View according to Baldini**[29]**.**

### Randomization

Patients who meet the inclusion criteria will be informed about the study by their orthopaedic surgeon at the Department of Orthopaedics of Martini Hospital Groningen. They will be informed about the treatment and the risk of complications according to the Dutch Medical Treatment Contracts Act. After consenting to participate, patients will be randomly assigned to one of the two regimens in a 1:1 ratio (Figure 2). The schedule for randomisation will be randomly generated using a computer before initiation of the study. To conceal the outcomes of the randomization, the allocation numbers will be put into concealed, opaque envelopes. An independent researcher will prepare the envelopes. Following informed consent, a randomization envelope will be opened. The randomisation allocation will not be notified to either the patient or the independent researcher, as both patient and investigator will be blinded to the outcome of the randomization.

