### Sample size calculation

Using the patellofemoral scoring system by Baldini et al.[30], the sample size is based on a mean difference of 10 points between both groups at 2-years follow-up. To detect this difference of 10 points with a standard deviation of 8 points, alpha of 5% and a power of 90%, a sample size of 18 patients in each study group is required. To compensate for potential drop-out and loss to follow-up, a total of 50 patients will be included in the study.

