### Statistical analysis

All statistical analyses will be computed using SPSS (IBM SPSS, Inc., Version 20.0, 2011). For the clinical parameters, t-tests will be used for continuous variables or the Mann–Whitney U-test when the variables are not normally distributed. A Chi-square test will be used for dichotomous variables. To assess differences in the results of the Baldini score and the KOOS over time between the two study groups, generalised estimating equations (GEE) analyses will be conducted. Longitudinal data are characterised by repeated observations of the same subjects. GEE analysis was developed to correct for repeated outcomes within the same subject[36]. With a GEE analysis, adjustments for the effect of differences in patient characteristics on the outcome variables can also be made by including these variables as covariates. Both an intention-to-treat analysis as a per-protocol analysis will be performed.

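### Operating surgeon is named neither in the allocation nor among the covariates; pre-specifying it as a two-level covariate would be a cheap, modest gain in precision

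*Protocol article*

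**What the plan says.** Under Study design, the protocol article states: "Two orthopaedic surgeons will perform the procedure, and are thus not blinded". Under Randomization, "patients will be randomly assigned to one of the two regimens in a 1:1 ratio", and "The schedule for randomisation will be randomly generated using a computer before initiation of the study". No stratification factor, block or list structure is given there.

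Under Statistical analysis, group comparisons of clinical parameters use t-tests or Mann-Whitney tests, and chi-square tests for dichotomous variables. The Baldini score and the KOOS are analysed over time by GEE. On covariates the section says that "adjustments for the effect of differences in patient characteristics on the outcome variables can also be made by including these variables as covariates". The baseline variables listed under Data collection methods are age, gender, BMI and severity of OA. The operator appears in none of these places.

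The Baldini patellofemoral score is the primary outcome. On the planning target, the Sample size calculation section says that "the sample size is based on a mean difference of 10 points between both groups at 2-years follow-up". Its other inputs are an SD of 8, 5% alpha and 90% power; it arrives at 18 per arm and sets total enrolment at 50.

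**The concern.** The randomised difference is an operative step, and each operation is done by one of two people. The document itself gives two reasons why their results might differ. The Intervention section leaves the execution of the patellar resection and its coverage to the operator. According to the Abstract, patellofemoral arthritis, which is an entry condition, is judged by the treating surgeon, so case mix could differ by surgeon.

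If the surgeons' mean Baldini scores differ and their cases fall unevenly between arms, part of the surgeon difference is counted as a resurfacing effect in that trial. Even with a perfectly even split, an analysis without a surgeon term leaves the between-surgeon variance in the residual and widens the confidence interval. The operator is known for every case, and using it costs almost nothing.

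**Working it through.** **Inputs from the protocol article.** Two surgeons (Study design); 1:1 allocation (Randomization); target difference 10 points, SD 8, alpha 5%, power 90%, 18 per arm, 50 enrolled (Sample size calculation). Two-sided testing is assumed.

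**Inputs assumed.** Cases split 25:25 between surgeons, arms of 25, no stratification by surgeon, and a difference D between the surgeons' mean scores of 2, 4 or 8 points. The document gives no value for D or for the case split.

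**1. The plan's own figure.** n per arm = 2 × (1.960 + 1.282)² × 8² / 10² = 13.5, so 14; the t-test calculation gives 15. The stated 18 is not reproduced at 90% power. It corresponds to a t-test at 95% power. The stated number is therefore conservative, which is a separate matter, but it sets the margin available here: power is about 95% at 18 per arm and 99% at 25 per arm.

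**2. Chance imbalance of surgeons.** Let X be the number of surgeon A's 25 cases that fall in one arm; X is hypergeometric (50, 25, 25). The difference between arms in A's share is (2X − 25)/25.

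- SD of the difference = (2/25) × √(25 × 0.5 × 0.5 × 25/49) = 0.143
- P(difference ≥ 20 points, i.e. 15 v 10 or worse) = 0.258
- P(difference ≥ 28 points, i.e. 16 v 9 or worse) = 0.089
- With cases split 70:30 or 80:20 between surgeons, the SD falls to 0.131 or 0.114.

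**3. Shift in the realised contrast.** Shift = D × imbalance. The standard error at 25 per arm is 8 × √(2/25) = 2.26. The last column is the simulated rejection rate of the unadjusted t-test when there is no treatment effect, given exactly a 28-point imbalance. Where a range is shown, it covers the SD of 8 excluding or including the surgeon component.

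| D | Shift at 20 points | Shift at 28 points | Shift at 28 points / SE | Rejection rate given 28 points |
|---|---|---|---|---|
| 2 | 0.4 | 0.56 | 0.25 | 5.5% |
| 4 | 0.8 | 1.12 | 0.49 | 7% |
| 8 | 1.6 | 2.24 | 0.99 | 11–13% |

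Given a 20-point imbalance, the rejection rates are about 5%, 6% and 7%.

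**4. Averaged over all randomisations.** In 6,000 simulated trials per setting, the unadjusted estimate was centred on the true effect and its type I error was 4.7–5.4%.

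**5. Precision and power.** If surgeon variance comes on top of SD 8, total SD = √(64 + D²/4).

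| D | Total SD | Surgeon share of variance | Unadjusted power, 18/arm | Unadjusted power, 25/arm |
|---|---|---|---|---|
| 2 | 8.06 | 1.5% | 95.1% | 99.0% |
| 4 | 8.25 | 5.9% | 94.2% | 98.7% |
| 8 | 8.94 | 20% | 90.3% | 97.2% |

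The unadjusted interval is wider by a factor of total SD / 8: about 1%, 3% and 12%. With a surgeon term, simulated power is about 99% at N = 50 and 94–95% at N = 36 for all three values of D. When D = 0, the unneeded term lowers simulated power from 95.2% to 94.6% at N = 36 and from 99.2% to 99.1% at N = 50.

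**The case against.** The strongest reply is that the document contains no wrong statement on this point. It is a condensed article. It does not say that the schedule is a single unrestricted list, and its sentence on covariates is permissive, not a closed list. A reader might infer that the surgeon was ignored in the trial. The text does not support that, since a fuller protocol or analysis plan could stratify or adjust. What stands is narrower: the text shown makes no provision for surgeon, and the only class of covariates it names does not include the operator.

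A reader might also infer that the resurfacing estimate is biased or the test invalid. That does not follow. Over randomisations the shift has mean zero, the ordinary standard error already covers it, and type I error stays near 5%. The higher rejection rates in step 3 hold only given an unusually uneven split.

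Nor is the trial underpowered for this reason. Even an assumed 8-point difference leaves 90% power at 18 per arm. If the planning SD of 8 already contains surgeon variation, nothing is lost against the plan.

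The size also depends on assumptions. Imbalance is 12 points or less in about 74% of trials, giving shifts of at most 0.5 points (D = 4) or 1.0 point (D = 8). A full-SD gap between two surgeons in one department is extreme, because approach, prosthesis, denervation and rehabilitation are common to all patients. These points stand, and they make the matter minor. They do not remove the case for a nearly free covariate whose inclusion is best settled before the data are seen.

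**Conclusion.** The point holds as a minor improvement. As written, the analysis has no surgeon term, so a chance imbalance of surgeons goes into the single estimate the trial will report, and between-surgeon variance stays in the error. Under the assumed 25:25 case split, an imbalance of 20 points or more is expected in about one trial in four, and of 28 points or more in about one in eleven. At 28 points the shift is 0.6 to 2.2 points for surgeon differences of 2 to 8 points. That is 6 to 22% of the 10-point target and at most about one standard error.

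The gain on offer is modest: better precision, and an estimate that corrects for whatever split occurs. If the surgeons hardly differ, there is almost nothing to gain and almost nothing to lose.

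**What to change.** Pre-specify operating surgeon as a fixed two-level covariate in the GEE models for the Baldini score and the KOOS, and in the KSS comparison. For the KSS this means a linear model with arm and surgeon in place of the plain t-test. The cost is one degree of freedom per model. The covariate should be the surgeon assigned before the envelope is opened, so that it is a baseline variable; one sentence in the plan can state this. This part can be adopted even if allocation has already begun.

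If allocation has not started, a separate envelope list for each surgeon, with permuted blocks of varying size not disclosed to the surgeons, is an optional addition. It costs a second list and makes allocations slightly more predictable. That matters somewhat here because patients are informed about the study by their orthopaedic surgeon and the operating surgeons are not blinded. The covariate alone is sufficient.

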### Intervention

All patients will be operated using the medial parapatellar approach and will receive a posterior cruciate ligament retaining all cemented total knee prosthesis (AGC^®^ Total Knee System, Biomet, USA). Patella denervation and osteophyte resection will be performed in all patients with or without resurfacing[9, 10, 31]. In the patellar resurfacing group the patella will be resected to the appropriate size. The posterior articulating surface will be removed with the patella everted laterally. The resection will begin just below the subchondral bone at a level, which corresponds to the thickness of the patella component to be implanted. The aim of this procedure is to ensure maximum coverage of the cut surface without implant overhang. The one-peg all-polyethylene patellar prosthesis will be cemented in one stage with the tibial and femoral components. All patients will have the same postoperative rehabilitation regime.

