### Secondary study parameters/endpoints

Knee function will be assessed by means of two scoring systems: the Knee Society clinical rating system (KSS) and the Knee injury and Osteoarthritis Outcome Score (KOOS). The KSS is subdivided into a knee score that rates only aspects of the knee joint itself, such as range of motion and stability, and a functional score that rates the patient’s ability to walk and climb stairs[32].The KOOS is developed as an instrument to assess patients’ opinion about their knee and associated problems[33, 34]. The KOOS consists of 5 subscales; pain, other symptoms, function in daily living, function in sport and recreation, and knee-related quality of life, with scores ranging from 0 (worst) to 100 (best).

Component loosening, wear, and patellofemoral problems including fracture or loosening of resurfaced patellae, subluxation and wear of non-resurfaced patellae will be assessed on conventional weight-bearing radiographs and views according to Baldini[35]. The view according to Baldini is a dynamic weight-bearing axial radiographic view of the patellofemoral joint with the patient standing in a semi-squatting position with knees in 45 degrees of flexion (Figure 1)[29].

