**Flowchart of patient inclusion.**

### Data collection methods

Preoperatively as well as at six weeks, and six, 12,18 and 24 months postoperatively patient assessments will be performed. Age, gender, body mass index (BMI), severity of OA, will be recorded preoperatively. Perioperative complications will be registered. Primary and secondary outcome measurements will be obtained at all time points by an independent investigator (Table 1).

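### As written, the blinded assessor's remit takes in radiographic outcomes that reveal the arm, and the article states no rule keeping those films from the assessor before the 24-month score

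*Protocol article*

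**What the plan says.** Under Study design, the article gives outcome evaluation to one person: "One independent investigator, not involved with enrollment or surgical procedure, will evaluate the outcome measurements". It then promises: "This investigator and all patients will remain blinded through the assigned regimen". The two operating surgeons are stated not to be blinded.

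Under Data collection methods: "Primary and secondary outcome measurements will be obtained at all time points by an independent investigator", with a pointer to Table 1.

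Under Secondary study parameters/endpoints, after the KSS and KOOS, radiographic outcomes are listed, some for the prosthesis in general and some for the patella. For the patella the list reads: "fracture or loosening of resurfaced patellae, subluxation and wear of non-resurfaced patellae will be assessed on conventional weight-bearing radiographs". The Baldini view is used as well, and the article describes it as follows: "The view according to Baldini is a dynamic weight-bearing axial radiographic view of the patellofemoral joint".

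The primary outcome is the Baldini patellofemoral score, 0 to 100, which mixes objective and subjective elements (Main study parameter/endpoint). The hypothesis and the sample size both refer to this score at 24 months.

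The safeguard stated under Randomization is that neither the patient nor the independent researcher is told the allocation.

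**The concern.** Some of the radiographic outcomes are defined by the treatment received. To grade loosening of a patellar component, the reader must see that there is one; to grade wear of a native patella, the reader must see that it is native. The reading itself therefore discloses the arm. If the person who does this also examines the patient and completes the Baldini score and the KSS, the promise of blinding cannot be kept for later visits.

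At stake is the part of the primary score that rests on the examiner's judgement. The surgeons already know the allocation, so the independent assessor's blinding is what protects this part of the comparison. Once lost, it cannot be restored in the analysis, because a scoring bias between arms looks the same as a treatment effect.

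**Working it through.** The plan gives no figure on this point, so the check is mainly a side-by-side reading.

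**Step 1. Who evaluates what.** Study design assigns outcome evaluation to one blinded investigator and makes no exception for radiographs. Data collection methods has an independent investigator obtain primary and secondary outcomes. The Methods section headed as secondary endpoints contains the radiographic outcomes. Joined, these three statements put the radiographic outcomes within the blinded assessor's remit.

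**Step 2. Whether the films reveal the arm.** Both arms receive the same femoral and tibial components. In one arm the patella is also resected and fitted with a component: "The one-peg all-polyethylene patellar prosthesis will be cemented in one stage with the tibial and femoral components". In the other the patella is left in place. The Baldini view images this joint, and some outcome definitions differ by resurfacing status. A reader who applies them learns the arm.

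**Step 3. When the films are taken (Table 1).**

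| Postoperative visit | Knee AP/lateral and Baldini view | Baldini score, KSS, KOOS |
|---|---|---|
| Week 6 | yes | yes |
| Month 6 | no | yes |
| Month 12 | yes | yes |
| Month 18 | yes | yes |
| Month 24 | yes | yes |

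Scoring before viewing the films on the same day could keep the week-6 score blinded. It could not protect the month-24 score if the films from week 6, month 12 and month 18 had already been read by the same person.

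**Step 4. Whether the stated safeguard is enough.** Not notifying the assessor of the allocation prevents disclosure from the randomization record. It does not prevent disclosure from a radiograph. The article describes no separate film reader, no order of scoring and reading, and no restriction on access to films or the operation report.

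**Step 5. Illustration of what a bias could do.** The size of any bias is an assumption; nothing in the document supplies it. Inputs from Sample size calculation: SD 8, alpha 5% (taken as two-sided, since the sidedness is not stated), 18 per group, and 50 patients in total, which at 1:1 is 50/2 = 25 per group. The 18 is used only as the plan's own number; this point does not depend on how it was obtained.

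For a two-sample t-test with no true effect and a scoring bias of b points between arms, the noncentrality is b / (SD × √(2/n)), with 2n − 2 degrees of freedom.

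- n = 18: standard error 8 × √(2/18) = 2.67. For b = 2, noncentrality 2/2.67 = 0.75; for b = 3, 3/2.67 = 1.125.
- n = 25: standard error 8 × √(2/25) = 2.26. For b = 2, noncentrality 2/2.26 = 0.88; for b = 3, 3/2.26 = 1.33.

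Probability of a significant result (5% without bias):

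| Assumed bias | 18 per arm | 25 per arm |
|---|---|---|
| 1 point | 6.5% | 7.2% |
| 2 points | 11.3% | 13.9% |
| 3 points | 19.4% | 25.5% |

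Biases of 2 and 3 points are 2/10 = 20% and 3/10 = 30% of the 10-point target difference. The table shows how sensitive the comparison would be; it does not estimate what would happen.

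**The case against.** The strongest reply is that no sentence says the blinded assessor reads, or can see, postoperative films. The link depends on joining a phrase under Data collection methods to a section heading, and there are reasons not to join them. The abstract names only KSS and KOOS as secondary measures and treats radiographs in a separate sentence. The investigator is said to work at all time points, yet month 6 has no film, so the sentence fits the clinical scores better than the radiographs. Table 1 keeps films and scores in separate columns. The only film reader named anywhere is the treating surgeon, for the preoperative views. A condensed article may also leave the details of film reading to the full protocol.

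Much of this stands. A reader might infer that blinding is lost from week 6 and that every later primary score is given by someone who knows the arm. The document does not support that: it would require both that the assessor reads the films and that they are read as they are taken, and neither is stated. Batch reading at the end, or a different reader, is compatible with the text.

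A reader might also infer that any bias would favour resurfacing, because the Discussion says a significant difference is expected. That passage gives the authors' reasons for the patient selection and the measurement tool; it does not show what the independent assessor believes.

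What does not fall away is the conflict in wording. The point does not rest on an omitted operational detail. The article gives outcome evaluation to one blinded person without exception, and its own Methods count arm-revealing radiographic outcomes among the secondary endpoints. If another person reads the films, the statement under Data collection methods is too broad and should be corrected.

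**Conclusion.** The point holds conditionally and with moderate confidence. Followed literally, the Methods have one investigator both stay blinded and obtain outcomes that cannot be graded without learning the arm. If that person reads the films as they are taken, the examiner-rated part of the primary score would be unblinded before the 24-month assessment on which the hypothesis and sample size rest. Non-notification of the allocation does not prevent this. The article does not establish that it will happen.

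The size and direction of any resulting bias cannot be derived from the document. The article does not say how many of the 100 points are examiner-rated; that the objective part is rated by the examiner is a reading of its description of the score. The false-positive rates above rest entirely on an assumed bias. The KOOS records the patient's own opinion and is not directly exposed to the assessor's knowledge.

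**What to change.** State that the blinded investigator completes the Baldini score and the KSS at every visit without access to postoperative radiographs or the operation report, and that study radiographs are read in batch only after the last month-24 clinical score is locked. The same investigator can then do both. Routine clinical viewing of films stays with the operating surgeons, who are unblinded already.

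If someone else already reads the films, correct Data collection methods to say so, limit the blinded investigator's task to the clinical scores, and make the abstract and the Methods agree on whether radiographic outcomes are secondary endpoints.

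The cost is some wording and a data-access rule, with no extra staff or visits. The downside is that research readings of the radiographs become available only at the end.
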